### Statistical analysis plan

2.7

Baseline characteristics and study outcomes will be summarized using descriptive statistics. The normality of continuous variables will be assessed using the Shapiro-Wilk test and visual inspection of histograms and Q-Q plots. Continuous variables with a normal distribution will be presented as means ± standard deviations (SD), while non-normally distributed variables will be reported as medians and interquartile ranges (IQR). Treatment effects will be reported as the estimated mean difference (MD) between groups with 95% confidence intervals (CIs) to provide a clear estimation of the effect size. Categorical variables will be expressed as frequencies and percentages (n, %). Baseline differences between groups will be assessed using one-way ANOVA or Kruskal-Wallis tests for continuous variables, and Chi-square tests or Fisher’s exact tests for categorical variables.

The analysis will be conducted according to the Intention-to-Treat (ITT) principle, including all randomized participants (N = 105) for both primary and secondary endpoints. To address missing data arising from participant withdrawal, Multiple Imputation by Chained Equations (MICE) (m=20 imputed datasets) will be performed prior to the primary analysis. Treatment effects will be evaluated using analysis of covariance (ANCOVA). The post-intervention measurements will be included as the dependent variable. Fixed effects will include group (HIIT, MICT, LHIIT), and the baseline measurements will be included as a covariate. The results from the imputed datasets will be pooled using Rubin’s rules. Tukey’s Honestly Significant Difference test will be used for *post-hoc* pairwise comparisons. Furthermore, sensitivity analyses for primary outcome will be conducted to assess the robustness of the results. These will include: (1) a Per-Protocol analysis; (2) an analysis excluding participants with >5% body weight change; and (3) an analysis including percentage body weight change as a covariate in the primary ANCOVA model. All statistical analyses will be performed using R software (version 4.5.1). A two-sided p-value< 0.05 will be considered statistically significant.

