### Randomization

2.3

A stratified block randomization method will be employed in this study. Participants will be randomly assigned to the following three groups: MICT group (n=35), HIIT group (n=35), and LHIIT group (n=35). Stratification is based on sex (male and female) and age. Stratification will be based on participant gender (Male, Female) and age group (18–30 years and 31–45 years), resulting in four distinct strata. Within each stratum, a computer-generated randomization sequence will be created using permuted blocks of size 6. The randomization list was generated prior to study commencement using R 4.5.1. To ensure allocation concealment, sequentially numbered, opaque, sealed envelopes will be prepared in advance based on the stratified randomization list. Following eligibility confirmation and informed consent, the research coordinator allocated the participant to the treatment group indicated in the next available envelope within the appropriate stratum.

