### Sample size

2.6

The sample size is calculated based on the primary comparison between the HIIT and MICT groups regarding the absolute change in MRI-PDFF from baseline to 12 weeks. Based on the previous study that implemented a similar intervention duration, we anticipated an absolute reduction in hepatic fat content of -1.7% (SD 1.1%) for the HIIT group and -0.9% (SD 0.7%) for the MICT group (22). Assuming a pooled standard deviation of 0.92% and a two-sided significance level of 0.05, a sample size of 28 participants per group is required to achieve 90% statistical power to detect the between-group difference. To account for a potential dropout rate of 20%, the sample size is adjusted to 35 participants per group. Consequently, a total of 105 participants will be recruited, with equal allocation (1:1:1) to the HIIT, MICT, and LHIIT groups.

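### The primary ANCOVA leaves out the stratification factors, sex and age group; if these predict 12-week hepatic fat beyond baseline, the test is conservative and a little power is lost

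*Protocol article*

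**What the plan says.** Section 2.3 (Randomization) of the protocol article restricts the allocation: "Stratification will be based on participant gender (Male, Female) and age group (18–30 years and 31–45 years), resulting in four distinct strata". It continues: "Within each stratum, a computer-generated randomization sequence will be created using permuted blocks of size 6".

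Section 2.7 (Statistical analysis plan) takes the post-intervention value as the dependent variable and names the model terms: "Fixed effects will include group (HIIT, MICT, LHIIT), and the baseline measurements will be included as a covariate". There is no term for sex, age group or stratum. Of the three sensitivity analyses, only one changes the covariates: "an analysis including percentage body weight change as a covariate in the primary ANCOVA model". That variable is measured after randomisation and is not a stratification factor. No other section adjusts for the strata.

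**The concern.** Blocking within strata makes the arms nearly equal in sex and age mix, so these factors contribute little to the chance difference between arms. A model without them still counts the variation they cause as residual error. The standard error it reports then describes a less balanced design than the one used. Intervals come out wider than they need to be, and the test rejects less often than its nominal level.

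The investigators judged sex and age worth balancing, and the analysis does not use that choice. With only 28 evaluable participants per arm planned, precision that costs almost nothing is worth taking. How much is at stake depends on how strongly the two factors predict the outcome once baseline hepatic fat is in the model.

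**Working it through.** **Inputs.** From section 2.6 (Sample size): expected changes of "1.7% (SD 1.1%) for the HIIT group and -0.9% (SD 0.7%) for the MICT group", a difference of 1.7 − 0.9 = 0.8 percentage points; "Assuming a pooled standard deviation of 0.92% and a two-sided significance level of 0.05, a sample size of 28 participants per group"; and "To account for a potential dropout rate of 20%, the sample size is adjusted to 35 participants per group". *Assumption:* R² is the share of the outcome variance left after baseline that sex and age group explain. The documents give no value, so 0 to 0.15 is tabulated.

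**Reproducing the plan's figures.**
- Pooled SD = √((1.1² + 0.7²)/2) = 0.92.
- n per arm = 2 × (0.92/0.8)² × (1.960 + 1.282)² = 27.8, rounded up to 28.
- Dropout: 28/(1 − 0.20) = 35.
- Power at 28 per arm is 90.2% by normal approximation and 89.2% by noncentral t.

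The stated sizes hold without any gain from covariates.

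**Formulas.** The model without strata reports SE = 0.92 × √(2/28) = 0.246, so 0.8/SE = 3.254. With exact balance within strata, the true SD of the estimate is SE × √(1 − R²) under either model. Hence:
- Type I error without strata = 2 × [1 − Φ(1.96/√(1 − R²))]
- Power without strata = Φ((3.254 − 1.96)/√(1 − R²))
- Power with strata = Φ(3.254/√(1 − R²) − 1.96)

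| R² | SE ratio, without/with strata | Type I error without strata | Power without | Power with | Gain (points) |
|---|---|---|---|---|---|
| 0 | 1.00 | 5.0% | 90.2% | 90.2% | 0 |
| 0.05 | 1.03 | 4.4% | 90.8% | 91.6% | 0.8 |
| 0.10 | 1.05 | 3.9% | 91.4% | 92.9% | 1.6 |
| 0.15 | 1.08 | 3.4% | 92.0% | 94.2% | 2.2 |

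Gains are taken before rounding.

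**Simulation, no dropout.** 84 evaluable participants, three arms, blocks of 6 in four strata, 6,000 runs per setting.
- At R² = 0 both models have 88.9% power.
- At R² = 0.05, type I error without strata is 4.8%; power is 88.8% without and 89.7% with them.
- At R² = 0.10, the mean reported SE without strata is 0.247 against a true SD of about 0.235. Type I error is 3.8% without and 4.7% with strata; power is 90.1% and 91.8%.

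**Simulation with dropout.** The table assumes exact balance, which incomplete blocks and dropout erode. With 105 randomised, 84 random completers and 60% of participants assumed in one level of each factor (6,000 runs), type I error without strata is 4.8%, 4.1% and 4.0% at R² of 0.05, 0.10 and 0.15. The power gains are 0.9, 2.0 and 2.7 points. Monte Carlo error is about 0.3–0.4 points.

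**If Tukey's HSD governs HIIT versus MICT.** Section 2.7 names it for pairwise comparisons. The critical value rises from about 1.99 to about 2.39, and power at 28 per arm falls to about 81%. In simulation (4,000 runs per setting), adding the strata raised power from 80.7% to 82.1% at R² = 0.05, from 80.9% to 84.4% at 0.10 and from 80.5% to 86.0% at 0.15.

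**The case against.** The strongest reply is that the harm is conditional and small. It exists only if sex and age group predict the outcome beyond baseline hepatic fat, and the documents give no figure for that. At R² = 0 the two models perform alike. The error runs in the safe direction, and the sample size was set with an SD of 0.92 and no covariate gain. All of this stands, and it limits the weight of the point.

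A reader might infer that the precision bought by stratifying is lost. It is not. The design reduces the true variance of the estimate under either model; only the reported standard error fails to show it.

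A reader might also compare power with the strata to the plan's 90.2% and read off gains of 1.4 (91.6 − 90.2), 2.7 (92.9 − 90.2) and 4.0 (94.2 − 90.2) points. That nearly doubles the effect, because stratification also raises the power of the model without strata, as the table shows.

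It could be said that a condensed article need not list every term and that a separate analysis plan may add the strata. This is weaker: section 2.7 names the dependent variable, the fixed effect and the covariate, and then refers to that model as the primary ANCOVA. The reply does hold for the imputation model. Its variables are not listed, so nothing shows that the strata are left out there, and no fault is claimed.

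**Conclusion.** The point holds in a limited, conditional form. The strata restrict the randomisation and are absent from the named terms of the primary model. If they explain 5–15% of the residual variance (an assumption), the type I error is roughly 3.4–4.8% instead of 5%. The lower end assumes exact balance within strata; the upper end comes from the simulations. Including the strata would gain about 1–3 power points at 28 evaluable per arm with a 0.05 test not corrected for multiplicity, and about 1–6 points if Tukey's HSD applies to HIIT versus MICT. If they explain nothing, the loss is nil.

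The documents do not support reading this as bias, as false-positive inflation or as a failure of the sample size: 28 and 35 per group both reproduce. It is a low-cost improvement in precision and does not threaten the validity of the trial.

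**What to change.** In section 2.7, add sex and age group (18–30, 31–45 years) as fixed effects to the ANCOVA for the primary and secondary outcomes, before any outcome data are seen by arm. Both variables are already known at randomisation. The cost is one line of text and two degrees of freedom: with 84 evaluable participants the residual falls from 84 − 4 = 80 to 84 − 6 = 78. Naming the terms now also removes room for a later, data-driven choice of covariates. The sample size needs no change.

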### Research design

2.1

This trial is a single-center, three-arm, open-label randomized controlled study (**Figure 1**). As a superiority trial, a non-exercise control group will not be included, given that numerous studies have already demonstrated the significant efficacy of aerobic training for decreasing HFC in individuals with MASLD. A total of 105 eligible participants aged 18–45 years will be randomized in a 1:1:1 ratio to the high-intensity interval training (HIIT) group, moderate-intensity continuous training (MICT) group, or low-volume HIIT (LHIIT) group. The intervention will last 12 weeks. The HIIT and MICT groups will perform exercise sessions aiming for approximately 400 kcal per session (~1200 kcal/week), while the LHIIT group will perform shorter sessions of approximately 200 kcal per session. To minimize confounding factors, all participants will receive standardized dietary guidance to maintain a stable caloric intake consistent with their baseline habits during the intervention period. All exercise sessions will be supervised by certified exercise trainers to ensure adherence, safety, and fidelity to the protocol. Due to the nature of the interventions, participants and trainers cannot be blinded; however, outcome assessors, imaging analysts, and statisticians will remain blinded to allocation. The primary outcome is the change in HFC, quantified by magnetic resonance imaging–proton density fat fraction (MRI-PDFF), with the primary comparison set between HIIT and MICT. Analyses involving the LHIIT group are considered exploratory and will be interpreted as hypothesis-generating. This trial protocol has been reviewed and approved by the Ethics Committee of the First Affiliated Hospital of Naval Medical University (CHEC2025-253) and registered on the Chinese Clinical Trial Registry (ChiCTR2500107821). Any modifications to the protocol will be fully documented and described in detail in subsequent publications.

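### The primary HIIT-MICT test takes its error variance partly from the exploratory LHIIT arm, so its standard error and power depend on an SD the plan does not give

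*Protocol article*

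**What the plan says.** Section 2.1 makes HIIT versus MICT the primary comparison and sets the third arm apart: "Analyses involving the LHIIT group are considered exploratory and will be interpreted as hypothesis-generating".

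Section 2.6 sizes the trial on the primary comparison alone. It anticipates changes in MRI-PDFF of minus "1.7% (SD 1.1%) for the HIIT group and -0.9% (SD 0.7%) for the MICT group", then combines the two SDs: "Assuming a pooled standard deviation of 0.92% and a two-sided significance level of 0.05". From this it concludes that "a sample size of 28 participants per group is required to achieve 90% statistical power to detect the between-group difference", raised to 35 for 20% dropout. No SD is given for LHIIT.

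Section 2.7 gives one model for all comparisons, an ANCOVA of the post-intervention value: "Fixed effects will include group (HIIT, MICT, LHIIT), and the baseline measurements will be included as a covariate". It follows this with Tukey's HSD for pairwise comparisons and a two-sided 0.05 threshold. It names no robust or arm-specific variance, and it does not exempt the primary contrast from Tukey.

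**The concern.** A standard ANCOVA estimates one residual variance from all arms, and Tukey's HSD uses that same estimate. Equal arm sizes protect a two-arm comparison from unequal variances, because the pooled variance then equals the average of the two that matter. They do not protect a pairwise contrast whose error term also averages in a third arm. The plan's own SDs for the two primary arms differ by a variance ratio of 1.21/0.49 = 2.5, so the question is not purely theoretical.

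What is at stake is the one confirmatory result. If LHIIT scatters less than the average of HIIT and MICT, the model's standard error for HIIT-MICT is too small. If LHIIT scatters more, it is too large. The SD of 0.92 behind the sample size is a two-arm figure and is not, in general, the SD that the section 2.7 test will use.

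**Working it through.** **Inputs.** Section 2.6: SDs 1.1 and 0.7, difference 1.7 - 0.9 = 0.8, two-sided alpha 0.05, 28 per arm after dropout. Assumed, because the protocol does not give it: LHIIT SD of 0.5, 0.7, 0.92 or 1.1.

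**1. The plan's own figure.** Pooled SD = sqrt((1.21 + 0.49)/2) = sqrt(0.85) = 0.92. Then n = 2(1.96 + 1.2816)² × 0.92²/0.8² = 2 × 10.51 × 0.8464/0.64 = 27.8, so 28, and 28/0.8 = 35. The figure is reproduced. (The noncentral t gives 89.2% power at 28.)

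**2. True variance against model variance.** With n per arm and LHIIT variance v:

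- true variance of HIIT minus MICT = (1.21 + 0.49)/n = 1.70/n
- variance the three-arm model uses, on average = 2(1.70 + v)/(3n)
- ratio of standard errors = sqrt[((1.70 + v)/3)/0.85]

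The ratio is 1 only when v = 3 × 0.85 - 1.70 = 0.85, that is, an LHIIT SD of about 0.92.

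**3. Error and power.** Simulation of the contrast, 28 per arm, 1,000,000 runs per setting, no covariate. Critical |t| at 81 df is 1.990 unadjusted and 2.388 for Tukey. Power is for a true difference of 0.8.

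| LHIIT SD | Pooled three-arm SD | SE ratio | Type I, Tukey | Power, Tukey | Type I, unadjusted | Power, unadjusted |
|---|---|---|---|---|---|---|
| 0.5 | 0.806 | 0.874 | 4.1% | 87.4% | 8.7% | 93.2% |
| 0.7 | 0.854 | 0.927 | 3.0% | 84.8% | 6.9% | 91.8% |
| 0.92 | 0.921 | 0.999 | 2.0% | 80.3% | 5.0% | 89.4% |
| 1.1 | 0.985 | 1.068 | 1.3% | 75.5% | 3.7% | 86.7% |

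The closed form 2(1 - Φ(1.96 × ratio)) gives 8.7%, 6.9%, 5.0% and 3.6% for the unadjusted column, in agreement. A test on HIIT and MICT alone gives 5.1% error and 89.0% power in every row.

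**4. With a baseline covariate.** Fitted three-arm ANCOVAs (35 per arm, 20,000 runs per setting, baseline SD 6 and slope 0.9 assumed) give 4.1%, 3.0%, 2.0% and 1.3% with Tukey, and 8.8%, 7.1%, 5.2% and 3.8% unadjusted.

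**5. Separating the two effects.** At LHIIT SD 0.92 the pooling is neutral, so the drop from 89.4% to 80.3% (9.1 points) is Tukey's multiplicity penalty. Moving the LHIIT SD to 1.1 costs a further 80.3 - 75.5 = 4.8 points; moving it to 0.5 returns 87.4 - 80.3 = 7.1 points. These shifts come from the variance pooling alone. Between the two ends, the average standard error, and with it the interval width, changes by a factor of 1.068/0.874 = 1.22 although nothing about HIIT or MICT has changed.

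**The case against.** **The written test is conservative.** A reader might infer from the unequal SDs that the planned analysis has a type I error anywhere from 4% to 9%. The protocol does not support that. Those figures belong to an unadjusted contrast, and Tukey's HSD is the only pairwise test section 2.7 names. Under Tukey with equal arms, error reaches 5% only if the LHIIT SD falls to about 0.3, with a ceiling of 5.7% as that SD nears zero. It can pass 5% with fewer HIIT participants (5.4% with 28 HIIT, 35 in each other arm and LHIIT SD 0.5). This objection stands, and it moves the cost from false positives to power and to an unstable standard error.

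**The inflation side needs an SD the plan does not give.** This also stands. The nearest anchor in the text points the other way. The Discussion (section 3) describes the study cited in section 2.6 as low-volume HIIT with 89% more fat reduction than MICT, and 1.7/0.9 = 1.89 matches. The SD of 1.1 therefore appears to come from a low-volume arm. At LHIIT SD 1.1 the test is conservative on either reading.

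**Sections 2.6 and 2.7 do not contradict each other.** This is correct. Section 2.6 quotes two SDs but plans on a common one, which fits a common-variance model. The SDs are also for change scores, not ANCOVA residuals, and the type I calculation combines them with equal means. They are nevertheless the plan's only variance information and the basis of its power.

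**Variance estimation can be left to the SAP.** This stands only in part. Section 2.7 states the model, factor levels, covariate and pairwise test, so this is a stated choice that can be judged. That it names no robust variance is not in itself a fault.

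**Conclusion.** The point holds in a limited form. In standard form, the section 2.7 analysis makes the standard error, interval and power of the HIIT-MICT comparison depend on an arm that section 2.1 calls exploratory. The standard error is right, on average, only if the LHIIT SD happens to be about 0.92.

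Under the section 2.6 SDs, 28 per arm and an assumed LHIIT SD of 0.5 to 1.1, the planned Tukey test has 4.1% down to 1.3% type I error and about 87% down to 75% power, below the stated 90% throughout. Part of that shortfall is multiplicity adjustment and not variance pooling. The documents do not show that the planned test inflates type I error. Inflation, up to 8.7% in this range, would arise if the contrast were read unadjusted from the same three-arm model and LHIIT scattered little. For that reason the multiplicity rule and the variance should be settled together.

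The result rests on the assumed LHIIT SD and on the 1.1 and 0.7 reflecting a real difference in variance. It is a worthwhile and inexpensive improvement, not a fatal flaw.

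**What to change.** In section 2.7, define the primary HIIT-MICT contrast on its own, at two-sided 0.05, with a variance that does not depend on LHIIT. Either fit the ANCOVA to those two arms only, or keep the three-arm mean model and use HC3 or arm-specific residual variances. Keep Tukey, if wanted, for the exploratory LHIIT comparisons. In section 2.6, state that power refers to this contrast: about 89% at 28 per arm.

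Of the two options, arm-specific or HC3 variance is safer if dropout differs between arms. With 28 HIIT and 35 MICT, a pooled two-arm test has about 6.3% error, against about 5.0% for a Welch-type test. Imputing by arm keeps LHIIT scatter from returning through the imputation model; with HC3 and within-arm imputation, simulated error was 4.5% to 4.9% and power about 87%.

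Cost: one or two sentences, standard R functions, and no change to sample size or conduct. The downside is a few residual degrees of freedom, and at most about 1 point of power if the three variances prove equal.

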### Compliance and adherence

2.8

At enrollment, all participants will receive standardized education to ensure full understanding of the intervention requirements and the importance of adherence. Exercise sessions will be delivered under direct supervision by certified exercise trainers, with adherence monitored through detailed attendance records and continuous heart rate tracking. To enhance participant adherence and motivation, participants will receive personalized feedback on their progress from the researchers, and will be contacted via text message or phone calls if they miss more than one session. Furthermore, to maintain consistency in habitual dietary intake, participants will be required to complete a 3-day dietary record (two weekdays and one weekend day) using a mobile application every two weeks. These logs, including food logs and meal photographs, will be reviewed by a study dietitian, who will provide immediate feedback if average daily energy intake deviates by more than $10\%$ from the established baseline level.

Adherence will be quantified as the proportion of prescribed sessions attended and completed within the target training intensity zone. The minimum adherence threshold for inclusion in the per-protocol analysis is set at 70%. Participants whose adherence falls below this level will receive additional counseling and behavioral support from the research team. If adherence remains inadequate despite these measures, withdrawal from the trial may be considered. All cases of withdrawal and their reasons will be documented and transparently reported in the final trial outcomes.

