### Safety

2.9

This trial will be conducted in accordance with the Declaration of Helsinki and established clinical research guidelines. Prior to enrollment, all participants will provide written informed consent after being fully informed of the potential risks and benefits of participation. Baseline health assessments will be performed by qualified physicians to confirm eligibility and ensure participants’ suitability for exercise testing and interventions. Throughout the intervention period, participants’ health status will be closely monitored, with systematic documentation of any safety-related information, including modifications to the exercise regimen, participant-reported symptoms, and monitoring results. Additionally, the trial will be immediately discontinued for any participant presenting with: (a) SBP > 180 mmHg or DBP > 110 mmHg; (b) exercise-induced angina or dyspnea; (c) syncope or dizziness; or (d) severe musculoskeletal injury. Any affected participant will receive appropriate medical treatment. Emergency medical support will be available on site during all exercise sessions.

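### Section 2.8 allows participants to be withdrawn from the trial, not only from training, for low adherence, so an obtainable primary outcome can be lost and then imputed, against the ITT principle

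*Protocol article*

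**What the plan says.** Section 2.8 (Compliance and adherence) measures adherence as the share of prescribed sessions that were both attended and completed in the target intensity zone. It adds: "The minimum adherence threshold for inclusion in the per-protocol analysis is set at 70" (per cent). People below that level receive counselling and support, and then: "If adherence remains inadequate despite these measures, withdrawal from the trial may be considered". On what follows withdrawal it says only: "All cases of withdrawal and their reasons will be documented and transparently reported in the final trial outcomes".

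Section 2.7 (Statistical analysis plan) describes the analysis as ITT, "including all randomized participants (N = 105) for both primary and secondary endpoints". The missing-data method is tied to withdrawal: "To address missing data arising from participant withdrawal, Multiple Imputation by Chained Equations (MICE) (m=20 imputed datasets) will be performed". The ANCOVA is then specified: "Fixed effects will include group (HIIT, MICT, LHIIT), and the baseline measurements will be included as a covariate".

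The study schedule (Table 2) and Section 2.4.1 place MRI-PDFF at baseline and week 12 only. Section 2.9 (Safety) says that "the trial will be immediately discontinued for any participant presenting with" certain events.

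**The concern.** ITT needs more than a full list of randomised participants. It needs their outcomes to be sought whatever they did with the intervention. Section 2.8 names the trial, not the training, as the thing a poor adherer may be withdrawn from, and Section 2.7 names withdrawal as the source of the missing data to be imputed. A participant who would willingly attend the week-12 scan could therefore be removed and have the primary outcome imputed.

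Three features of this trial make that matter.

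- **The trigger differs by arm.** Adherence is scored against the intensity zone. Section 2.5 sets this at 45–55% of heart rate reserve for MICT, and at 70–90% for the HIIT work intervals with recovery at 40%.
- **The decision is discretionary and not shielded from allocation.** Section 2.1 states that trainers cannot be blinded, and they supervise the sessions in which adherence is recorded. No criterion is given beyond adherence remaining inadequate, and the article does not say who decides.
- **No interim liver-fat value exists.** With scans only at weeks 0 and 12, a withdrawn participant contributes no on-study PDFF to the imputation.

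At stake is whether the HIIT-MICT difference describes all those randomised or something closer to those who kept training.

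**Working it through.** **The plan's own figure.** Section 2.6 gives reductions of 1.7 (SD 1.1) for HIIT and 0.9 (SD 0.7) for MICT. The difference is 1.7 − 0.9 = 0.8 points, and the pooled SD is √((1.1² + 0.7²)/2) = 0.922. With SD 0.92, two-sided α 0.05 and 90% power, the normal approximation gives 2 × (1.960 + 1.282)² × (0.92/0.8)² ≈ 27.8, so 28 per arm. Allowing for 20% dropout, 28/0.8 = 35. Both stated figures reproduce, so the sample size is not in question.

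**Bias illustration.** The documents give neither a withdrawal fraction nor the response of those withdrawn, so both are assumed.

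- p_H and p_M: fractions withdrawn in HIIT and MICT (assumed 5% or 20%; of 35 per arm, about 2 or 7 people).
- r: the share of the arm's effect that withdrawn people truly keep (assumed 0 or 0.5).
- Mean reduction in those who remain: the planned 1.7 and 0.9.
- Imputation ignores adherence and returns the arm mean.

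With arm mean m, the true mean over everyone randomised is m(1 − p) + r·m·p, whereas imputation returns m. The arm's reduction is overstated by (1 − r)·p·m. The shift in the HIIT-MICT difference is therefore

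(1 − r) × (1.7·p_H − 0.9·p_M).

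| Withdrawn HIIT / MICT | Shift, r = 0 | Share of 0.8 | Shift, r = 0.5 |
|---|---|---|---|
| 5% / 5% | 0.085 − 0.045 = +0.04 | 5% | +0.02 |
| 20% / 20% | 0.340 − 0.180 = +0.16 | 20% | +0.08 |
| 20% / 5% | 0.340 − 0.045 = +0.295 | 37% | +0.1475 |
| 5% / 20% | 0.085 − 0.180 = −0.095 | −12% | −0.0475 |

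A positive shift overstates the HIIT advantage and a negative one understates it. The shift is zero when p_M/p_H = 1.7/0.9 ≈ 1.9, and also when r = 1, that is, when those withdrawn respond like those who stayed.

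**The case against.** Several stronger readings are tempting, and the document does not support them.

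- **That the imputation treats withdrawn people as adherers.** Section 2.7 does not list the imputation variables, and an article may leave these to the analysis plan. Table 2 schedules adherence and anthropometric measures at weeks 4 and 8, and Section 2.5 adds exercise tests at both, so useful predictors will exist. A per-protocol set defined by a 70% threshold also implies that some people below it remain with observed outcomes, and these can inform the imputation. The bias claim is therefore conditional.
- **That the ITT analysis set is contradicted.** It is not, because all 105 are analysed. The conflict is with the principle.
- **That removal depends on liver-fat response.** The team cannot see that response before week 12. Removal depends on adherence, which may be related to it.
- **That HIIT is bound to be favoured, or by as much as 37%.** The 20% figure is the planning allowance for dropout of any cause. Assigning all of it to adherence withdrawals with no benefit at all is close to a worst case, and the 20%/5% split has no source. The last row of the table reverses the sign.
- **That Section 2.9 discards outcomes.** Its criteria are mostly acute events, and the wording may mean only that exercise stops. It is ambiguous, no more.
- **That the lack of a sensitivity analysis on the missing-data assumption is a fault.** None of the three listed varies it, but an analysis plan could add one, so it is not part of this point.

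It is also fair to say that withdrawal is optional, follows counselling, and may be rare in a supervised 12-week programme, and that nothing expressly cancels the week-12 scan. What survives is that the point does not rest on silence alone: Section 2.8 states the rule, and Section 2.7 expects withdrawal to produce missing data. A later analysis plan can improve the imputation but cannot recover a scan that was never taken.

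**Conclusion.** The concern holds as a conflict between a stated conduct rule and the ITT principle. The protocol permits the trial itself to make an obtainable primary outcome missing, for a post-randomisation reason measured against different targets in each arm, with no interim PDFF to support the imputation.

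The resulting bias cannot be given a single size or direction. Across the four assumed patterns with no retained effect it runs from −0.095 to +0.295 points against the planned 0.8, and it halves if those withdrawn keep half the effect. These figures assume that adherence plays no part in the imputation model. Including it would reduce the problem but need not remove it.

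**What to change.** - In Section 2.8, delete withdrawal from the trial as a consequence of low adherence. Nothing analytic is lost, because the 70% threshold already keeps poor adherers out of the per-protocol set.
- State that participants who stop or reduce training remain in follow-up and are invited to the week-12 MRI-PDFF and other assessments unless they withdraw consent.
- Name sessions completed as a predictor in the MICE model in Section 2.7.
- Reconcile the wording of Section 2.9 so that it is clear whether discontinuation refers to exercise or to outcome collection. The safety criteria themselves are not at issue and stay as they are.

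The cost is a wording change plus the effort of bringing back a few non-adherent participants for a visit that the schedule already contains. It should be made as early as possible, because each scan missed under the present wording is lost for good.
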